## Methods/Design

### Participants and setting

#### Testicular cancer patients

30 patients with disseminated germ cell cancer, scheduled to initiate 3 cycles of BEP-chemotherapeutic treatment at Rigshospitalet, Copenhagen, will be included in the study. Further inclusion and exclusion criteria are listed in table 1. The TC patients will be included and baseline-tested before the start of the first cycle of BEP treatment.

**Table 1 T1:** Eligibility Criteria

Inclusion Criteria
Age: 18-45
Ability to read and understand Danish
Signed informed consent
Exclusion criteria
Presence of any type of current or previous malign disease
Presence of any type of cardiovascular disease (i.e. Cardiomyopathy, Coronary heart disease etc.)
Presence of any type of chronic disease (i.e. Diabetes mellitus, Chronic Obstructive Pulmonary Disease etc.)

#### Healthy control subjects

15 healthy control subjects, matching TC patients in the following parameters: age, BMI and exercise training history, will be included in the study. This intervention-arm will represent the "standard" effect of HIPRT in young men not affected by antineoplastic treatment. The study will be conducted according to the CONSORT (Consolidated Standards of Reporting Trials) statement for non-pharmacological interventions[6], and has been approved by the Regional Ethics committee for the Capital Region (protocol nr: H-1-2010-049) and the Danish Data Protection Agency (jr.nr. 2010-41-5118).

### Recruitment

The study flow is presented in Figure 1. TC patients (subjects) will be recruited by clinicians at the Department of Oncology, Rigshospitalet, Copenhagen. The primary attending oncologist will present oral and written information about the study to the eligible participant. Interested participants will be contacted by the study coordinator, who will answer any further questions. The participants will be invited to visit the training facilities, before giving their written consent.

**Figure 1 F1:**
[figure not shown]
**Study Flow**.

The healthy control subjects will be recruited through announcements in local newspapers and the internet.

### Randomization

Following the baseline test, TC patients will be allocated to either, STRength training (STR, n = 15), receiving a 9-wks HIPRT-program during treatment, or UNTrained (UNT, n = 15), who will receive standard care. The randomization procedure used is a simple adaptive biased-coin randomization. The inclusion criteria (men, aged 18-45, same diagnosis/stage of disease and treatment protocol) secure comparable groups in terms of sex, age and disease profile at baseline, and therefore no stratification will be carried out. The healthy CONtrol subjects (CON, n = 15) will be allocated to HIPRT without randomization.

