### Sample size

Sample size is chosen to ensure significant muscular hypertrophy, evaluated by mean fiber area, in CON, among whom a 15% increase is estimated according to earlier studies.

N > (1,28*√(0.15*0.85))^2^/(0.15^2^) = 9,28. A minimum of 10 is required in each group, but due to clinical experience concerning possible drop out due to medical reasons 15 are included in each group.

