### Analytic Plan

1-way repeated measures Analysis Of Variance (RM-ANOVA) will be used to evaluate test-data within groups for assessments at baseline, 9 and 21 weeks. 2-way ANOVA (group × time) will be used to test the effect of HIPRT for TC patients (STR vs. UNT), and BEP-treatment for training response (STR vs. CON) respectively. The equivalent non-parametric tests will be used for mRNA expression and protein levels. Significance level of 0.05 is chosen.

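### Eligibility criteria do not make two arms of 15 comparable, and the group × time ANOVA for STR vs UNT is a less precise use of the baseline value than a covariate would be

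*Protocol article*

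**What the plan says.** The Randomization section allocates patients after the baseline test, 15 to STR and 15 to UNT: "The randomization procedure used is a simple adaptive biased-coin randomization". It argues that the inclusion criteria "secure comparable groups in terms of sex, age and disease profile at baseline, and therefore no stratification will be carried out".

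The Analytic Plan fixes the between-group model: "2-way ANOVA (group × time) will be used to test the effect of HIPRT for TC patients (STR vs. UNT") and, separately, STR vs CON. It names no covariate. Its within-group sentence lists baseline, 9 and 21 weeks as the assessments, so baseline is read here as a level of time. Non-parametric equivalents are foreseen for mRNA and protein levels.

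Table 2 schedules biopsy, blood sample, DXA, strength tests and questionnaires at baseline. The Sample size section allows for losses: "A minimum of 10 is required in each group, but due to clinical experience concerning possible drop out due to medical reasons 15 are included".

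**The concern.** Two statements are at issue.

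- **The rationale.** An age limit of 18 to 45 and a shared treatment plan restrict who enters. They do not make the two arms alike in age or disease profile. The allocation method as described acts on arm sizes, not on patient characteristics. The text also relies on a common stage, while Table 1 lists no stage criterion; the Participants section requires disseminated disease and three planned cycles.
- **The model.** STR vs UNT is the only randomised comparison, and the sample size was set for hypertrophy within CON, not for this contrast. Precision is therefore scarce. A change-score comparison implicitly fixes the slope on baseline at 1, whereas the slope best supported by the data is normally smaller. The cost is variance and, when the arms differ at baseline by chance, an estimate pushed in the opposite direction.

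**Working it through.** **Inputs from the document:** 15 per randomised arm (Randomization); minimum of 10 per group (Sample size); age 18 to 45 (Table 1); alpha 0.05 (Analytic Plan), taken as two-sided. **Assumptions:** equal SD at baseline and 9 weeks, rho from 0.3 to 0.9, and an effect of 0.8 SD. The document gives none of these three.

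**1. The plan's own figure.** "N > (1,28*√(0.15*0.85))^2^/(0.15^2^) = 9,28". Recomputed: (1.28 × √0.1275)² / 0.0225 = 9.28, rounded up to 10. It reproduces. It contains no SD or rho and concerns CON, so it gives no information on the precision of STR vs UNT.

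**2. Chance imbalance.** The standard error of a standardised baseline difference is √(2/n).

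- n = 15: √(2/15) = 0.365; P(difference above 0.5 SD in either direction) = 17%.
- n = 10: √(2/10) = 0.447; the same probability is 26%.

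For age, assume a uniform distribution over 18 to 45. The SD is 27/√12 = 7.8 years and the standard error at n = 15 is 7.8 × 0.365 = 2.85 years. Mean ages then differ by more than 3 years in 29% of trials and by more than 5 years in 8%.

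**3. Precision at 9 weeks.** In units of σ², and up to the common factor 2/n, the variance of the contrast is 2(1−rho) for change scores and 1−rho² for ANCOVA. The ratio is (1+rho)/2. Power by normal approximation is Φ(0.8/√(variance × 2/15) − 1.96). For example, at rho 0.5 the change-score variance is 1, so 0.8/0.365 − 1.96 = 0.23 and power is 59%.

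| rho (assumed) | Variance ratio | Power, change score | Power, ANCOVA |
|---|---|---|---|
| 0.3 | 0.65 | 46% | 63% |
| 0.5 | 0.75 | 59% | 72% |
| 0.7 | 0.85 | 81% | 87% |
| 0.9 | 0.95 | 99.8% | 99.9% |

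With 10 per arm and rho 0.5, power is 43% against 54%.

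**4. Small-sample check.** The ratios above ignore the cost of estimating the slope, which multiplies the ANCOVA variance by 1 + 1/(2n−4) on average: 1.038 at n = 15 and 1.063 at n = 10. At n = 15 the ratios become 0.675, 0.779, 0.883 and 0.987. A simulation with t-based tests (100,000 trials per setting, 15 per arm) gives power of 43% against 58%, 56% against 67%, 78% against 83%, and 99.7% for both. At rho 0.9 and 10 per arm the ratio is 0.95 × 1.063 = 1.01, so the gain is gone.

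**5. Over-correction.** Given a baseline difference D, the change-score contrast is shifted by −(1−rho)D. With D = 0.5 SD and rho 0.5 the shift is 0.25 SD against the arm that starts higher. In 40,000 simulated null trials with 15 per arm, restricted to those with an imbalance above 0.5 SD, the change-score test rejected in 11.8% (rho 0.5) and 9.0% (rho 0.7), and ANCOVA in 5.1% and 5.0%. Over all trials the change-score test rejected in 5.0% and 4.9%.

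**The case against.** Much of the opposing case stands, and it limits the point.

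- A reader might infer that the plan makes no use of baseline. It does: with baseline as a time level, the group × time term compares changes. The criticism is only that baseline is not a covariate.
- A reader might infer that the randomised test is invalid. It is not. Type I error is about 5% over all trials, and the inflation in step 5 is conditional on an imbalance having occurred.
- The Randomization section claims comparability only in sex, age and disease profile. It says nothing of fibre area, strength, BMI or training history, and should not be faulted as if it did.
- CON was chosen by "matching TC patients in the following parameters: age, BMI and exercise training history". This might be read as an admission that STR and UNT should be stratified on the same factors. It is not: CON is not randomised, so matching is its main protection, while the randomised arms have allocation.
- With 30 patients only one or two strata would be workable, and fibre area from stored biopsies might not be read in time. Omitting stratification is defensible; only the reason given for it is not.
- A condensed article may leave a covariate list to a fuller plan. That is fair, so the point rests on the model the article does name and on a statement it does make.
- The gain depends on an unknown rho and is negligible when rho is near 0.9.

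**Conclusion.** The point holds as one of efficiency and of an unsound rationale, not of validity. Eligibility secures sex but not balance in age or disease profile. Imbalances above 0.5 SD on a given variable are expected in about one trial in six at 15 per arm and one in four at 10.

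The change-score contrast gives up about 35%, 25%, 15% and 5% of variance at rho 0.3, 0.5, 0.7 and 0.9, somewhat less after the small-sample correction. These figures rest on assumed rho, equal SDs at the two times and, for power, an assumed 0.8 SD effect; they apply to the 9-week contrast, not to a joint test over three assessments. The direction favours ANCOVA over most of that range, with little or nothing to lose at its upper end.

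**What to change.** - For the continuous outcomes, state that the 9-week STR vs UNT contrast is estimated by ANCOVA with the participant's own baseline value of that outcome as covariate, or by a repeated-measures mixed model with a common baseline mean for the two randomised arms.
- For mRNA and protein levels, where the Analytic Plan foresees non-parametric tests, use the same model on a log or rank scale.
- Delete the statement that the inclusion criteria secure comparable groups. The decision not to stratify can stand without it.

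The cost is wording in the analysis plan. The outcome baselines are already scheduled, so no patients, visits or assays are added. Fixing the model before the data are seen also avoids choosing an adjustment after an imbalance appears.

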### Blinding

Blinding of participants in this type of study is not possible since participants will know whether they are exercising or not. Nor are the training instructors blinded, since they will know if they are instructing a patient undergoing chemotherapy or a healthy control subject. However, study personal doing baseline, post-intervention and follow-up assessment will be blinded, as will laboratory personal analyzing invasive biological samples (blood and muscle samples). Only the study coordinator and leading oncologist will know which TC patients are allocated in which groups.

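### The study coordinator speaks to interested patients before consent and also knows past allocations, so under the unstratified biased coin the next arm is partly predictable to that person while enrolment is still open

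*Protocol article*

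**What the plan says.** Three sections of the protocol article bear on this.

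- **Recruitment.** Clinicians do the recruiting: "TC patients (subjects) will be recruited by clinicians at the Department of Oncology, Rigshospitalet, Copenhagen". The treating doctor comes first: "The primary attending oncologist will present oral and written information about the study to the eligible participant". The coordinator follows: "Interested participants will be contacted by the study coordinator, who will answer any further questions". The section ends with: "The participants will be invited to visit the training facilities, before giving their written consent". Read in order, the coordinator's contact comes before consent.
- **Randomization.** Patients are allocated after the baseline test, 15 to STR and 15 to UNT. The method is given in one sentence: "The randomization procedure used is a simple adaptive biased-coin randomization". Because the inclusion criteria are held to make the groups comparable, "therefore no stratification will be carried out". The healthy controls are not randomised.
- **Blinding.** Assessors and laboratory staff are blinded. Patients and instructors are not. On who holds the allocations: "Only the study coordinator and leading oncologist will know which TC patients are allocated in which groups".

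The article does not state the coin's probability or rule, who runs the draw, who decides eligibility, or whether the leading oncologist enrols patients.

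**The concern.** A biased coin limits imbalance by making the lagging arm more likely. The price is that anyone who knows the tally knows which arm is favoured next. That does no harm if the person with the tally never meets candidates. Here the coordinator has both the tally and a conversation with each interested man before he signs. There are no strata and the patients come from one hospital, so a single running balance covers all 30.

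At stake is who enters each arm. A coordinator who expects the next man to go to STR may, without intending it, be more encouraging to a keen man than to a hesitant one, and the reverse when UNT is favoured. Blinded assessment protects the measurements and not the composition of the arms. STR versus UNT is the only comparison protected by randomisation, and at about 15 per arm a few influenced decisions are a noticeable share of a group.

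**Working it through.** **Step 1: the roles, side by side.**

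| Role | Contact with candidates before consent | Knows past allocations |
|---|---|---|
| Attending oncologist | Yes (Recruitment) | Not listed as knowing (Blinding) |
| Study coordinator | Yes (Recruitment) | Yes (Blinding) |
| Leading oncologist | Not stated | Yes (Blinding) |

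Only the coordinator is shown to have both. The overlap is written into the article; it is not inferred from silence.

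**Step 2: how predictable the next arm is.** The plan gives no figure on this, so there is none to reproduce.

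Inputs from the document: N = 30 randomised patients, two arms, no stratification.

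Assumptions:
- The coin probability p for the arm that is behind is 0.60, 2/3 or 0.75, with 0.5 when the arms are level. As an alternative, an urn-type coin gives each arm a probability equal to the other arm's share of past allocations.
- The guesser knows every past allocation and always picks the smaller arm.
- No other patient is allocated between the conversation and the draw.

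For a fixed coin, a guess is right with probability 0.5 when the arms are level and p when they are not. Let U be the expected number of the 30 draws made with unequal arms. Then

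expected correct guesses = 30 × 0.5 + (p − 0.5) × U.

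U comes from following the distribution of the imbalance draw by draw. With p = 2/3 it starts like this:
- Draw 1: the arms are level, so 0.500.
- Draw 2: the arms always differ, so 0.667.
- Draw 3: the arms are level with probability 2/3, so 2/3 × 0.5 + 1/3 × 2/3 = 0.556.

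Over all 30 draws:

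| Coin | U (share of 30) | Expected correct guesses | Rate |
|---|---|---|---|
| No knowledge of history | – | 15 | 50% |
| p = 0.60 | 23.25 (77%) | 15 + 0.10 × 23.25 = 17.3 | 57.7% |
| p = 2/3 | 21.52 (72%) | 15 + 0.1667 × 21.52 = 18.6 | 62.0% |
| p = 0.75 | 19.50 (65%) | 15 + 0.25 × 19.50 = 19.9 | 66.3% |
| Urn-type | – | 17.3 (direct recursion) | 57.5% |

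Knowing the history is therefore worth about 2 to 5 extra correct guesses in 30 (17.3 − 15 = 2.3; 19.9 − 15 = 4.9).

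**Step 3: sensitivity.** A stronger coin raises the rate: p = 0.80 gives 68.4% and p = 0.90 gives 72.1%. If exactly 15 per arm were enforced, the rates would be 61.3% (p = 0.60), 64.1% (p = 2/3) and 67.5% (p = 0.75), because the last allocations become certain once one arm is full.

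**Step 4: what the numbers do not give.** They measure predictability, not bias. Turning them into a shift in fibre area or another outcome would need the strength of any influence on consent, and the document offers no basis for that.

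**The case against.** The case on the other side has weight.

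- **Eligibility.** A reader might infer that the coordinator recruits patients or decides eligibility, and that the open-ended chronic-disease exclusion in Table 1 leaves that person discretion. The text does not support this. Clinicians recruit, and the man is already called eligible when the attending oncologist informs him, before the coordinator's contact. The exposure is to influence on consent only.
- **Leading oncologist.** A reader might also infer a second route through this person. The article gives neither that person's department nor any part in enrolment, so the route is possible but not shown.
- **Condensed article.** Who draws, how the draw is concealed and the coin probability may all be in the full protocol, and their absence is no finding. That stands. The point rests on what the article does say about the coordinator, although a safeguard recorded elsewhere would answer it.
- **Little room to steer.** Patients are already scheduled for chemotherapy, with baseline testing at days −5 to 0 and randomisation on day 1 (Table 2). A man can hardly be held back until a preferred arm is due. This limits the route to the tone and content of one conversation with a man who is already interested.
- **Baseline measurement.** The group × time analysis works on change from a pre-allocation baseline, so a plain difference in starting fitness would not count as a treatment effect. That is largely right. Selection on motivation or expected response to training would remain, because it acts on the change itself.
- **Leakage.** Training begins on day 1, and patients and instructors are unblinded, so clinicians may learn some allocations anyway. The fix reduces exposure and may not remove it.

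**Conclusion.** The point holds in a limited form. The article gives one person both pre-consent contact with candidates and knowledge of past allocations, under a method whose next result is partly predictable from those allocations. Predictability is about 58% to 66% against 50%, assuming a coin of 0.60 to 0.75 or an urn-type coin, the usual rule of favouring the lagging arm, and a guesser who uses the whole history. The article fixes none of these.

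A reader should not conclude that selection has biased or will bias the result. The document shows an avoidable opportunity, narrowed by the treatment schedule and by baseline measurement, and gives no means of sizing its effect. It merits correction because it touches the only randomised comparison and is cheap to remove.

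**What to change.** Separate the two roles among existing staff, in one of two ways:

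1. The coordinator keeps the pre-consent contact but does not see the allocation list while recruitment is open.
2. The coordinator keeps the list, and someone without access to allocations contacts interested patients before consent.

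In either case, each draw is made and held by an existing staff member who has no contact with candidates, and is released only after written consent and the baseline test. If the leading oncologist also enrols patients, the same separation applies to that role. Amend the Recruitment and Blinding sections accordingly. If such a safeguard is already in place, one sentence saying so settles the point.

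The cost is a reassignment of tasks, with no extra patients or procedures. Under the first option, training bookings for new STR patients would go through the allocation holder and the instructors, a small inconvenience given that training starts on day 1. With allocations hidden from whoever has pre-consent contact, that person's expected rate of correct guesses returns to 50% (15 of 30), apart from any arms learned informally.

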### Treatment

Antineoplastic treatment for TC patients consists of cisplatin 20 mg/m^2 ^and etoposide 100 mg/m^2 ^daily for 5 days and bleomycin 15.000 IU/m^2 ^given weekly. Three cycles of this combination are administered, with every cycle lasting three weeks.

### Intervention

The exercise intervention will be comprised of high intensity progressive resistance training (HIPRT) with 3 training sessions pr week, as previously described by Andersen and Aagaard [5]. In week 1 and 2 the participants will conduct 3 sets of 15 repetitions (reps) at a 15-repetition maximum (RM) intensity to become familiarized with the exercises. From week 3 and onwards, the participants will conduct 4 sets of 10 reps at 10-12 RM intensity. Progression will be assured, such that if the participant can do more than 12 reps, the weight will be increased. All exercises will be performed in a supervised setting to ensure correct technique and proper progression. This type of resistance exercise program has been proven to induce significant muscle hypertrophy in both healthy and diseased subjects [5].

#### Study arm 1: HIPRT for TC patients during and after BEP treatment (STR)

This group will conduct a 9 week HIPRT-program, initiated at day 1 of the treatment, and will be offered a 12 week rehabilitation-program after the course of chemotherapy.

#### Study arm 2: Usual care for TC patients during BEP treatment and HIPRT as rehabilitation following treatment (UNT)

This group will receive standard care for the 9 week period during treatment, and will be offered a 12 week rehabilitation-program with HIPRT after termination of chemotherapy.

#### Study arm 3: HIPRT for healthy matched control subjects (CON)

This group will conduct a 21 week HIPRT program following the same progression as STR.

### Study Endpoints and Assessment

During the course of the study the participants will carry out physical tests, have invasive biological samples taken and complete standardized questionnaires. The schedule for individual data assessment is presented in table 2, and the study endpoints are summarized in table 3.

**Table 2 T2:** Data Assessment Schedule

Data assessment	Baseline test Day - 5-0	Treatment start Day 1	2^nd ^cycle start Day 22	3^rd ^cycle start Day 43	Post interv. test Day 64-66	Follow-up test ~ Day 150
Muscle biopsy	x				x	x
Blood sample	x		x	x	x	x
DXA scan	x				x	x
Strength test	x				x	x
Questionnaires (SF 36 & EORTC)	x		x	x	x	x
Randomization		x				

**Table 3 T3:** Study Endpoints

Muscular morphology
• Mean fiber area
• Fiber type distribution
• Satellite cells
• Intracellular signaling molecules
Body Composition
• Lean Body Mass
• Fat percentage

Muscle strength
• Maximum Voluntary Contraction
• Leg Extensor Power

Systemic effects
• Cholesterol (TCHO, HDL, LDL, Triglycerides)
• Glucose
• Insulin
• Inflammatory markers (CRP, TNF-α, IL-6, IL-18)
• Anti-inflammatory markers (IL-4, IL-10)

Patient reported outcomes
• Health related Quality of Life (SF-36 and EORTC)

The healthy control subjects will carry out the same testing protocol and have the same biological samples taken, but will not receive cancer specific questionnaires.

